### Eligibility criteria

In this study, an individual will be defined as presumptive TB if he/she exhibits any of the following symptoms [26]:
Pulmonary TB: a cough for more than 2 weeks and at least one general symptomExtra-pulmonary TB: presence of symptoms, depending on the location of TB (e.g., enlarged lymph node, swollen backbone, swollen articulation, etc.), and at least one general symptomGeneral symptoms: fever, night sweats for more than 2 weeks, or unintentional weight loss (> 5% reduction in usual body weight over the last 6–12 months) [27]

Presumptive TB cases will be referred to the health centers for TB screening and diagnosis in the intervention arms and self-presented to the health centers in the control arm. We will include the aggregated number of cases diagnosed and notified from all arms regardless of age. However, we will only recruit people aged 18 years or older with TB (all forms) for the baseline and follow-up surveys and assessment of TB treatment outcomes.

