### Interventions

#### Explanation for the choice of comparators

The PCF strategy is a default setup in the national health system. PCF is a patient-initiated pathway that relies on the self-presentation of presumptive TB cases to the health centers to be diagnosed with TB. Upon screening by health center staff, sputum samples from presumptive TB cases belonging to the KAPs will be collected for examination by GeneXpert or direct smear microscopy if the GeneXpert system is not available. CXR will be performed at the referral hospital if the sputum examination result is negative. TB diagnoses will be made by clinicians based on clinical, radiological, and microbiological evidence. For presumptive TB individuals who present with cough for less than 2 weeks, CXR will be performed at the referral hospital, and sputum samples will be collected for GeneXpert testing if radiological abnormalities are detected [23]. For presumptive TB cases who do not belong to KAPs, smear examination will be performed if presenting with a cough lasting for 2 weeks or more. Those presenting to the health centers with cough for less than 2 weeks will be referred to the referral hospital for CXR, and cases with any radiological abnormalities will undergo smear examination [23]. Newly diagnosed people with TB will be treated and managed according to the national TB guidelines. We will follow-up all people with TB diagnosed during the study period for 6 months from the treatment initiation.

This is a patient-initiated pathway to TB diagnosis involving: a person with active TB experiencing symptoms that he or she recognizes as serious; a person having access to and seeking care, and presenting spontaneously at an appropriate health facility; a health worker correctly assessing that the person fulfills the criteria for presumptive TB; and the successful use of a diagnostic algorithm with sufficient sensitivity and specificity to diagnose TB.

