**Fig. 2 Fig2:**
[figure not shown]
Active case finding with a seed-and-recruit model. A network is built by seed, as illustrated by the dotted lines in the left panel. The network is expanded in a snowball fashion by recruiters who will be trained to recruit other people who might have tuberculosis (TB) in the community. We refer key populations for TB in this study to people aged 55 and above, people with diabetes, people living with HIV, household contacts of TB patients, and people who use and inject drugs. For GeneXpert test, one sputum specimen will be collected. For smear microscopy, three sputum specimens will be collected at three different times, over 2 days

All presumptive TB cases referred by seeds and recruiters will be screened by lay counselors using a symptoms screening questionnaire [17]. The screening for symptoms compatible with TB includes a cough lasting for at least 2 weeks, hemoptysis, fever, weight loss, and night sweats [17]. Presumptive TB cases and their symptoms screening questionnaire will be assessed by a nurse practitioner in the health center for further TB work-up. Those who are presumed to have TB will be asked to submit sputum samples at the health center for acid-fast bacilli examination. Sputum samples of KAPs will be assessed using the GeneXpert system at the referral hospital laboratory. For non-KAPs, direct smear microscopy will be undertaken at the nearest laboratory. If the sputum examination results are negative, further assessments and diagnosis of TB will be made on clinical and radiological grounds by clinicians. TB screening and treatment will be provided at the health facilities at no cost to the patient, in accordance with the policies of the NTP. Cases suspected of extrapulmonary TB (presence of local and general symptoms [23]) will be referred to the OD referral hospital for further assessment and diagnosis. We will follow-up all people with TB referred by seeds for 6 months from the treatment initiation.

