### Outcomes

We will measure the following endpoints in all four arms. The primary endpoint will be the case notification rate in the intervention and control ODs during the study period. We define a TB case to be either bacteriologically confirmed (smear-positive identified by smear microscopy, culture, or rapid diagnostics approved by the World Health Organization (WHO)), smear-negative TB (two sputum samples tested negative and clinically diagnosed by a clinician—with abnormal CXR or no improvement in response to a course of broad-spectrum antibiotics), or extrapulmonary TB (presence of local symptoms such as enlarged lymph nodes, joint swelling, and Gibbus deformity and presence of general symptoms such as cough, fever, weight loss, and night sweats) [23]. This will be ascertained from the results of the screening and routine case notification data reported to the NTP. We will also determine: additionality, comparing the yield in each arm with its respective historical baseline (same period in the preceding year); and cumulative yield over the project implementation period. Secondary endpoints will include: the number of people needed to screen to detect one TB case; direct and indirect costs per TB case notified; and the treatment outcome of all people with TB in this study. These data will be collected on the aggregated form at the health center level or as reported by the project implementation team in each arm, except cost data, which will be collected from study participants in the baseline and follow-up surveys.

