For the secondary endpoints, we will evaluate the treatment outcome of TB cases detected in this study according to the following categories: treatment completed (without evidence of failure); treatment failed (sputum smear remains positive at month 5 or later of treatment); died (death due to any reasons before and during treatment); lost to follow-up (people newly diagnosed with TB who do not initiate treatment or treatment course that is disrupted for 2 or more successive months); not evaluated (no treatment outcome data available); and cured (sputum smear converted from positive to negative in the final month of the treatment and on at least one earlier assessment at month 2 or month 5) [23]. The number needed to screen to detect one TB case in each arm will be calculated by dividing the total number of persons screened by the number of TB cases detected (i.e., the reciprocal of the absolute cumulative yield). Direct and indirect medical costs that will be incurred before and during health-seeking will be measured based upon the baseline and follow-up questionnaires. Costs for identification of presumptive TB cases and engagement with KAPs for screening, including training and meetings before initiating ACF activities, will be categorized separately from the costs for diagnosis using radiological/bacteriological means and management of people with TB. The incremental cost-effectiveness ratio (ICER) will be estimated by dividing the difference in total costs between trial arms by the difference in the total number of TB cases detected. The ICER per disability-adjusted life year averted will also be considered as a benchmark to determine whether the interventions are cost-effective.

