We will analyze the primary and secondary endpoints by intention to treat, and the analyses will be conducted in two stages. First, we will analyze and present primary and secondary endpoints using the cluster summary method. The baseline characteristics of all arms at the cluster level and individual-level characteristics at baseline and endline will be compared using Student’s *t* test and hierarchical or mixed-effect models to estimate the ratio of these means. As the ODs have several health centers, we will adopt a linear mixed-effects model adjusting for baseline measurements to account for clustering in the data. Individual-level data will also be incorporated into multivariable regression models to account for potential confounders differing by the trial arm and improve the precision of the risk ratios by accounting for intercluster variations. The impact of TB case-finding strategies on treatment outcomes will be evaluated using survival analysis to compare treatment success rates across the intervention and control arms. The study will be reported according to the Consolidated Standards of Reporting Trials (CONSORT) [33] statement (Additional file 3), the template for intervention description and replication (TIDieR) [34] checklist for intervention description and replication (Additional file 4), the Standard Protocol Items: Recommendations for Interventional Trials (SPIRIT) [35] statement (Additional file 5), and the Pragmatic Explanatory Continuum Indicator Summary-2 (PRECIS-2) [36] for pragmatic trials (Additional file 6). All statistical analyses will be conducted using STATA 14 (Stata Corp LP, TX, USA) and R (R Foundation for Statistical Computing, Vienna, Austria).

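### Survival analysis is a poor fit for treatment success, which is an end-of-course status, and the protocol describes the patients to be compared inconsistently across arms

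*Protocol article*

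**What the plan says.** Under Statistical methods for primary and secondary outcomes, the effect of case finding on "treatment outcomes will be evaluated using survival analysis to compare treatment success rates across the intervention and control arms". The same section sorts outcomes into six categories: cured, completed, failed, died, lost to follow-up and not evaluated. Death includes death before treatment, and loss covers "people newly diagnosed with TB who do not initiate treatment or treatment course that is disrupted for 2 or more successive months". Table 2 reads the outcome 6 months after treatment initiation. Outcomes says the data come on aggregated health-center forms or from the implementing team, and Table 1 lists treatment outcomes among the cluster-level assessments.

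On who is followed, the wording varies:

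- Control (Explanation for the choice of comparators): "We will follow-up all people with TB diagnosed during the study period for 6 months from the treatment initiation".
- Intervention 1: "We will follow-up all people with TB referred by seeds for 6 months from the treatment initiation".
- Intervention 2: the cases found in that arm, from the start of treatment.
- Intervention 3: follow-up 6 months from treatment initiation, with no population named.
- Outcomes: "the treatment outcome of all people with TB in this study".
- Table 2: all new patients.
- Eligibility criteria: the study will "only recruit people aged 18 years or older with TB (all forms) for the baseline and follow-up surveys and assessment of TB treatment outcomes".

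On analysis, the protocol states: "We will analyze the primary and secondary endpoints by intention to treat, and the analyses will be conducted in two stages". It continues: "First, we will analyze and present primary and secondary endpoints using the cluster summary method". Implementation places the whole population of each operational district (OD) in its cluster.

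**The concern.** Two things do not fit together.

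First, survival methods compare how fast an event occurs. Cure and completion are assigned when a course of set length ends, so their timing says little about whether treatment worked. Death, failure and loss rule success out. If they are handled as ordinary censoring, the method no longer estimates the proportion successfully treated. A clock that starts at treatment also gives no follow-up time to people who die first or never start, although the protocol counts both as unfavourable. Linkage to treatment after screening is one place where active and passive case finding could plausibly differ. Aggregated forms may not supply individual event times at all.

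Second, the followed patients are worded differently by arm. If the arm descriptions define the analysis set, actively found patients in intervention ODs would be compared with all patients in control ODs. That is a comparison of case mix and would break the promised intention-to-treat comparison of districts. The effect on treatment outcomes is a stated aim under Objectives, so the comparison matters even as a secondary endpoint.

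**Working it through.** The protocol gives no power or effect size for treatment outcome (Sample size covers the primary outcome only), so there is no figure to reproduce. The checks below are illustrations.

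**1. Success as the event, non-success censored.** Suppose success is recorded at one time. Let s be the proportion successful and r the proportion non-successful but still in the risk set then. With no earlier successes, 1 − KM = s/(s + r).

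- All non-successes gone beforehand (r = 0): 1 − KM = s/s = 1.00, for any s.
- s = 0.85, half of the 0.15 non-successes still at risk (assumed): 0.85/(0.85 + 0.075) = 0.919.
- s = 0.85, all still at risk: 0.85/(0.85 + 0.15) = 0.85, the true value.

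The distortion therefore depends on when unfavourable outcomes are recorded.

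**2. Simulation.** Assumed timings: success on days 180–210, death or loss on days 1–179; 20,000 patients per success level.

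| True success | 1 − KM at day 210, non-success censored | Cumulative incidence at day 210, non-success competing |
|---|---|---|
| 94% | 1.00 | 0.938 |
| 90% | 1.00 | 0.899 |
| 85% | 1.00 | 0.851 |
| 75% | 1.00 | 0.752 |

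At exactly day 180 both estimators are only about 0.03, because recording begins that day.

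One simulated data set with 3,000 per arm, clustering ignored:

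- 85% v 94% success, non-success censored: Cox HR 1.05, p = 0.08. The expected value is 1, because successes in both arms share the same recording days. The 9-point difference is missed.
- Same data, non-successes kept in the risk set: HR 0.78, p < 0.001.
- 94% v 94%, but completion recorded 14 days later in one arm: HR 0.21. Recording date alone looks like an effect.

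**3. Time origin at treatment start.** Take 94% success among starters (the national rate in Background and rationale) and assumed non-starting of 5% in control and 10%, 15% or 20% among actively found cases. Success among all diagnosed = 0.94 × (1 − non-start proportion).

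- Control: 0.94 × 0.95 = 0.893.
- Actively found: 0.94 × 0.90 = 0.846; 0.94 × 0.85 = 0.799; 0.94 × 0.80 = 0.752.

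From treatment start, both sides show 94%. With equal non-starting (5% in both) the comparison is 0.893 v 0.893, and no difference is hidden.

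**4. Who would be left out on the narrow wording.** Sample size gives additional notifications g of 110%, 98% and 30% from earlier implementation, and scenarios of 75%, 50% and 25%. Assume the extra cases are the actively found ones and passive detection is unchanged. The actively found share is w = g/(1 + g); the share left out is 1 − w.

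| g | w | Left out |
|---|---|---|
| 110% | 1.10/2.10 = 0.524 | 48% |
| 98% | 0.98/1.98 = 0.495 | 51% |
| 75% | 0.75/1.75 = 0.429 | 57% |
| 50% | 0.50/1.50 = 0.333 | 67% |
| 30% | 0.30/1.30 = 0.231 | 77% |
| 25% | 0.25/1.25 = 0.200 | 80% |

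In control ODs none would be left out. In Intervention 1 recruiters also refer cases, and the follow-up sentence does not name them, so a literal reading would leave out still more there.

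**5. Effect of following everyone.** With passive success at 94% everywhere, the OD difference is w × (actively found success − 0.94). If actively found success is 90% (assumed), −4.0 points becomes −4.0 × 0.524 = −2.1, −4.0 × 0.495 = −2.0 or −4.0 × 0.231 = −0.9.

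**The case against.** The best defence is that the protocol names only a family of methods. It does not say that success is the event or that unfavourable outcomes are censored, and such rules commonly sit in an analysis plan that is not shown. A competing-risk analysis is survival analysis too and recovers the success proportion. The first-stage cluster summary also covers this endpoint and could carry every category, including non-starters and pre-treatment deaths. On the population, Outcomes and Table 2 each give a single definition for all arms. The arm-level sentences may only describe contact for the follow-up survey, and the Intervention 2 wording can be read as all of that arm's cases.

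Much of this stands. A reader might infer that survival analysis cannot estimate success, or that its estimate would be near 100% whatever the truth. That needs non-success to be censored, which the protocol does not state, and to occur before completion. Failure can be assigned at month 5 or later and some patients will be not evaluated, so even then the figure may be lower (step 1). A reader might also infer that the followed patients do differ by arm and that the analysis is not by intention to treat. The documents conflict on this and do not settle it. Nor is the adult limit a source of bias between arms, since it applies to all arms alike.

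What the defence does not remove: the stated method suits a fixed-time status badly, the follow-up clock does not match the outcome categories, and the cluster summary stage does not say which patients enter it.

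**Conclusion.** The point holds as a mismatch of method and endpoint plus an internal contradiction about the analysis set. It should be corrected before analysis. It does not show that the planned result must be wrong.

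The size is conditional. Under ordinary censoring with all unfavourable outcomes before completion, the survival estimate reaches 100% at any true success rate and can miss a 9-point difference; under competing risks it does neither. If only actively found cases were followed in intervention ODs, 48% to 80% of their cases would be left out across the protocol's own effect assumptions, given that extra cases equal actively found cases. The event timings and non-start rates are assumptions, not document figures. Whether non-starting differs between arms is unknown.

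A limit remains whatever is chosen: the comparison is among diagnosed cases, a group that the intervention itself changes, so even with all cases included it is not free of case-mix differences.

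**What to change.** - Make the comparison one of proportions: treatment success (cured or completed) among all eligible TB cases notified in each OD, including those who never start treatment. Use the same population in every arm, and keep the 18-and-over limit in Eligibility criteria and apply it consistently.
- Count death, failure, non-starting, loss and not evaluated as non-success. Exclude not evaluated in a sensitivity analysis.
- Analyse by the OD-level cluster summary method already planned, or a binary mixed model.
- If a time-to-event analysis is kept, start time at diagnosis and treat unfavourable outcomes as competing events.
- Reconcile Eligibility criteria, Explanation for the choice of comparators, Interventions 1 to 3, Outcomes and Table 2 to this one set.
- Show actively found and passively found cases separately as a descriptive breakdown, and state that the comparison is among diagnosed cases.

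The cost is mainly wording, since health centers are already the source of outcome data. The downside is dilution: passively found cases in intervention ODs shrink any effect among actively found cases to about 0.52, 0.50 or 0.23 of its size for g of 110%, 98% and 30%.

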### Objectives

The primary aim of this study is to evaluate the effectiveness of ACF strategies in increasing the yield of TB diagnoses and case notifications in Cambodia. This study also aims to establish the effect of ACF strategies on TB treatment outcomes and to establish the number needed to screen to detect one TB case. Lastly, this study aims to estimate the cost-effectiveness of the interventions by measuring the cost per TB case identified and the incremental cost-effectiveness ratio.

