	Denominator: total number of individuals screened	Program data Provincial health department laboratory data to determine the number of people screened at health centers in the control arm
Secondary endpoints		
Treatment outcomes	TB treatment outcomes of all new patients 6 months after treatment initiation	Health centers
Number needed to screen	Numerator: total number of individuals screened	Program data Provincial health department laboratory data to determine the number of people screened at health centers in the control arm
	Denominator: number of cases reported by each arm	Program data Control arm: data to be collected from the health centers monthly
Cost per TB case diagnosed/notified	Direct and indirect medical costs while seeking care for TB Staff and intervention costs Diagnostics and medication costs	Health-care-seeking costs: data to be collected in the baseline and follow-up survey Intervention costs: data to be collected from KHANA, CENAT, and CATA DALYs: data to be extracted from WHO global burden of disease studies and other existing literature
Incremental cost-effectiveness ratio per DALY averted		

*CATA* Cambodia Anti-Tuberculosis Association, *CENAT* National Center for Tuberculosis and Leprosy Control, *DALY* disability-adjusted life year, *OD* operational district, *TB* tuberculosis, *WHO* World Health Organization

Data collectors (project staff from CATA, CENAT, KHANA, and/or health center staff) will be trained to explain the study to the participants, obtain written consent for the surveys (Additional file 2), and administer the questionnaire. The data collectors will brief participants on the nature and purposes of the study and potential risks, and will highlight that information will be kept confidential. Consent for the surveys will be taken by the data collectors in a private space after randomization.

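### The treatment-success comparison is conditional on being diagnosed, which ACF is meant to change, so it is not the intention-to-treat impact of case finding that the protocol calls it

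*Protocol article*

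**What the plan says.** The Objectives state a causal aim: "This study also aims to establish the effect of ACF strategies on TB treatment outcomes". In Statistical methods for primary and secondary outcomes, the analysis principle is "We will analyze the primary and secondary endpoints by intention to treat". The same section gives the method: "The impact of TB case-finding strategies on treatment outcomes will be evaluated using survival analysis to compare treatment success rates". The contrast itself is between arms; the plan is to "compare treatment success rates across the intervention and control arms".

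The people compared are defined more narrowly. That section says "we will evaluate the treatment outcome of TB cases detected in this study", and Eligibility criteria adds that, for the surveys and the treatment-outcome assessment, the trial will "only recruit people aged 18 years or older with TB (all forms"). Table 2 describes the endpoint as "TB treatment outcomes of all new patients 6 months after treatment initiation". By contrast, Implementation (under Assignment of interventions) places everyone living in a selected operational district (OD) in that cluster.

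The statistical section also plans multivariable regression on individual data to "account for potential confounders differing by the trial arm".

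**The concern.** Being detected happens after randomisation and is the event that the interventions exist to make more frequent. An ACF arm therefore contains people who would not have been diagnosed under passive case finding, and the control arm has no counterpart for them. Sorting diagnosed people by allocated arm keeps the arm labels but does not restore the comparison that randomisation created.

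If the extra cases have a different prognosis, the arms will differ in success even when ACF changes nobody's treatment result. A lower proportion could be read as harm while more people in the district are treated successfully; a higher one could be read as better treatment when only the case mix has moved. The causal aim in the Objectives, the impact wording and the intention-to-treat label all invite such readings.

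**Working it through.** **1. Randomised set against analysed set.** Randomised: all residents of the selected ODs (Implementation). Analysed: detected TB cases (Statistical methods), adults only (Eligibility criteria). Detection lies between the two and is the target of the intervention.

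**2. Do the documents expect the detected group to change?** Yes.
- Size: Sample size takes 110%, 98% and 30% more notified cases from earlier operations, with cautious scenarios of 75%, 50% and 25%.
- Make-up: control patients present themselves (Explanation for the choice of comparators). Intervention 1 works through referral and symptom screening. Intervention 2 invites household contacts, and neighbours who have symptoms. Intervention 3 X-rays everyone aged 55 or over, with or without symptoms. The change in case mix thus differs by arm.

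**3. Do the planned safeguards remove the selection?** The outcome categories count people who never start treatment as lost to follow-up, and deaths before treatment as deaths. That guards against selection at treatment start (although Table 2 times the endpoint from treatment initiation), but not at diagnosis. Regression handles measured covariates only.

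**4. How large could the artefact be?** The protocol gives no figure for treatment success by arm, so there is nothing to reproduce. Inputs:
- p0 = 0.94, success in passively found cases. Assumption: Background and rationale gives 94% as a national rate.
- f = 0.30, 0.98, 1.10, the proportional increase in cases (Sample size, scenario 1), assumed to apply to diagnosed adults; f = 0.25 is scenario 4.
- pa = success in the extra cases. Not in the documents; varied from 80% to 100%.
- No effect of ACF on any individual's treatment result. Assumption.

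Success among diagnosed in the ACF arm = (p0 + f × pa) / (1 + f), so the shift from p0 is [f / (1 + f)] × (pa − p0).

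| f | f/(1+f) | pa 80% | 85% | 90% | 94% | 98% | 100% |
|---|---|---|---|---|---|---|---|
| 25% | 20.0% | −2.8 | −1.8 | −0.8 | 0 | +0.8 | +1.2 |
| 30% | 23.1% | −3.2 | −2.1 | −0.9 | 0 | +0.9 | +1.4 |
| 98% | 49.5% | −6.9 | −4.5 | −2.0 | 0 | +2.0 | +3.0 |
| 110% | 52.4% | −7.3 | −4.7 | −2.1 | 0 | +2.1 | +3.1 |

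(Shifts in percentage points.) Extremes: (0.94 + 1.10 × 0.80) / 2.10 = 0.867, or −7.3 points; (0.94 + 1.10 × 1.00) / 2.10 = 0.971, or +3.1 points.

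**5. The same examples with a population denominator.** Ratio of successfully treated people = (p0 + f × pa) / p0. With pa = 0.85:
- f = 0.30: 1.195 / 0.94 = 1.27, while the proportion falls from 94% to 91.9%.
- f = 0.98: 1.773 / 0.94 = 1.89, while it falls to 89.5%.
- f = 1.10: 1.875 / 0.94 = 1.99, while it falls to 89.3%.

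**6. What the population rate cannot show.** If f = 0.30 and success dropped to 85% in every ACF-arm case, the ratio would be 1.30 × 0.85 / 0.94 = 1.18. The rate would still rise, so it mainly follows detection.

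**The case against.** Success among diagnosed patients, classified by guideline categories, is a legitimate programme measure, and this is a secondary endpoint. That stands: the fault lies in the causal and intention-to-treat labels, not in reporting the proportion.

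The size is illustrative. The national 94% is not tied to passive case finding and may include ACF-found cases, since the article describes ACF already running in Cambodia. Success in the extra cases is not documented, and with equal prognosis the artefact is zero. All of this stands.

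A population rate largely repeats the notification rate and does not answer whether treatment went better. This also stands, as step 6 shows, so the rate can only supplement the proportion.

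A reader might go further and infer that the comparison will show ACF as harmful, or that every ACF arm adds older people without symptoms. The documents do not support either: the sign depends on an unknown prognosis, and only the mobile-unit arm explicitly screens older people without symptoms. Nor can the population rate be assumed to come free from data already in hand. Outcome assessment is limited to adults, and the described follow-up covers all diagnosed people in the control arm, people referred by seeds in Intervention 1, and cases found in the arm in Intervention 2.

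**Conclusion.** The point holds as a mismatch between label and analysis. The protocol claims an intention-to-treat comparison and an impact of case finding, but specifies a contrast among people diagnosed after randomisation. Neither covariate adjustment nor the handling of non-starters changes that; the conclusion needs no numerical assumption.

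The size does need assumptions. With 94% success in passively found cases, no effect on anyone's treatment result, 30% to 110% more cases and 80% to 100% success among them, the artefact runs from about −7.3 to +3.1 points. The documents cannot fix where in that range it lies, or its sign. The case notification rate, whose denominator is the whole OD population, is untouched. The change should be made, but it does not threaten the trial's main comparison.

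**What to change.** 1. In Statistical methods for primary and secondary outcomes, describe treatment success among diagnosed people as a descriptive comparison conditional on diagnosis, and drop the intention-to-treat and impact labels for it. Align the Objectives wording.
2. Add, as a supplementary intention-to-treat measure, successfully treated cases (cured plus completed) per 100,000 OD population per year, analysed at cluster level like the notification rate. State that it combines detection with success, mainly reflects detection, and does not isolate treatment quality.
3. For that rate, use health-center outcomes for every case diagnosed in each OD in all arms. Reconcile the follow-up sets in Explanation for the choice of comparators, Interventions 1 and 2, and Outcomes (which refers to all people with TB in the study). Match the age range of numerator and denominator, given the adults-only rule in Eligibility criteria.

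Cost: the proportion loses its causal reading, and outcome records are needed for passively found cases in ACF districts, which the arm-specific follow-up wording may not cover. The new rate also rests on two ODs per arm, as the notification rate does.
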